| **Methods**: Population and Study Design  A single-center, randomized, double-blind, placebo controlled pilot study will be conducted in nonconsecutive HIV-1–infected patients aged 18 years or older.  Patients will be recruited at a tertiary care hospital (Institut Hospital del Mar d'Investigacions Mediques) in Barcelona, Spain.  All patients have chronic HIV infection, undetectable plasma viral load (,20 copies per milliliter) for at least 2 years, and a stable HAART regimen. It will be divided into 2 groups:  - Group 1 (n=22): Patients with CD4 +> 400 cells / ml and undetectable viral load for more than two years.  - Group 2(n=22): Discordant patients, deﬁned by an unfavorable persistent immunologic response (T-CD4+ cells <350 cells per microliter) despite long-term suppressed viral load (4-7 years).    Randomization:  A computer-generated randomization list will be used. Randomization will be performed by a hospital pharmacist unrelated to the care of the patients, using sequentially numbered containers. The participants and the care providers will be blinded after assignment to interventions.  Patients in both groups (1 and 2) will be randomized in 2 subgroups:  (A) 22 will receive daily oral *S. boulardii* supplementation for 3 months.  (B) 22 will receive white placebo patients (lactose) for 3 months.  Exclusion criteria:  - Patients who receive or have received in the last 6 months food supplements containing probiotics.  - Patients who have received antibiotic treatment in the last two months, or HIV patients who usually require to take antibiotics more than 2 times at year.  - Patients with presupposing poor adherence to dietary supplements or HAART.  - Changes in HAART regimen in the previous 2 years, and presence of a serious concomitant disease or substantial abnormalities in the laboratory tests that prevented study participation.  - Patients who do not sign the informed consent.  * Current antibiotic treatment during the study or the presence of any acute concomitant illness will not exclude patients out of the study.  **Intervention:**  - The intervention will be carried out an expert physician in Infectious Diseases.  - Daily treatment to all patients (S. boulardii VS placebo) will be prescribed at baseline in doses of 2 capsules every 12 hours, at least half an hour before intake, during 12 weeks.  - Extraction of blood samples and stool collection will be performed before starting probiotics (baseline) at 3 and 6 months.   In each case the following variables will be included in the data collection:  - Demographic affiliation, height, weight, toxic habits, depositional habit (BRISTOL scale).  - The HANDS scale of anxiety / depression will be apply.  - Dates of start and end of past and current antiretroviral medication will be recorded and concomitant medication administered during the study, including antibiotics.  - Any possible adverse effects of the intervention or serious adverse event will be recorded.  - Adherence to treatment will be registered, counting returned capsules on each visit.  **Study/Clinical Assessment:**  The primary end point of the study will be changes in serum LBP levels as a marker of microbial translocation.  Secondary endpoints will be as follows:   - Changes in markers of immune activity, including serum concentrations of soluble CD14 (sCD14), tumor necrosis factor alpha (TNF-a), interleukin 6 (IL-6), high-sensitivity C-reactive protein (Hs-CRP), B2 microglobulin, erythrocyte sedimentation rate, IL-2, IL-5, IL-12, D-dimer, IFN-Υ, ﬁbrinogen, Ig G, and Ig E. - Changes in immune status (T-CD4+ and T-CD8+ lymphocyte count) and HIV-viral load. - Analysis of gut microbioma by 16s rRNA sequencing. - Safety and tolerability.   **After screening for eligibility**, subjects will be visited at baseline (start of treatment), at week 12 (treatment discontinuation), and at week 24 (3 months after discontinuation of treatment).  Clinical and demographic data of the study patients will be collected from the medical records.  **At baseline**, eligible patients were randomized (1:1) to receive treatment with S. boulardii (2 capsules 3 times a day or 6 · 107 living bacteria) or placebo (2 capsules 3 times a day) for 12 weeks.  - Data collection: The data collected will be included in a database specifically designed for this protocol.  - Procedure:   - At each visit (Baseline, week 12 and week 24), clinical assessment and adverse events will be recorded, and blood samples were collected into 9 mL Vacuette serum separator tubes (Greiner Bio-One GmbH, Kremsmünster, Austria). Within 30 minutes after puncture, blood was centrifuged at 3000 rpm for 15 minutes, and serum samples were aliquoted and stored at 280°C until analysis. For all the tests, thawed serum samples were vortexed and centrifuged at 14,000 rpm for 10 minutes before testing. - All patients also provided 50gr of stool samples at each visit (Baseline, week 12 and week 24) , which will be stored at -80°C within the first 24-48 hours; to compare gut microbiome composition before and after a 12-week treatment with probiotic or placebo. - Once all samples will be collected, they will be sent together on dry ice to the Reference Laboratory of Catalonia, where they will be analyzed.   - Plasma and faecal sample Analysis:   - Inﬂammation Markers For analysis of IL-6 and TNF-a, the Milliplex MAP assay on a ﬂuorescent microsphere-based instrument (Merck Millipore, Merck KGaA, Darmstadt, Germany; Luminex/Bioplex200-Luminex Corp., Austin, TX and BioRad, Hercules, CA) will be used. Multianalyte proﬁling of serum concentrations will be performed using a commercially available multiplex immunoassay kit (HSCYTMAG-60K; Millipore, Billerica, MA). - Hs-CRP and b2 microglobulin will be measured using the Immulite chemiluminescent immunometric assay on its automated analyzer (Immulite One; Siemens Healthcare, Llanberis, United Kingdom). Plasma ﬁbrinogen will be measured using the Clauss coagulative method with HemosIL reactives (Instrumentation Laboratory, Bedford, MA). - Microbial Translocation Markers Serum levels of soluble CD14 will be quantiﬁed in duplicate with a commercially available enzyme-linked immunosorbent assay kit (Quantikine; R&D Systems, Minneapolis, MN) using a Quanta-Lyser 160 robotic workstation (Inova Diagnostics, San Diego, CA). - Serum LBP will be measured using the Immulite chemiluminescent immunometric assay on its automated analyzer. All assays will be performed according to the manufacturer’s instructions. - Fecal Microbiome Analyses:DNA will be extracted from frozen stool samples and amplified by PCR targeting 16S gene regions using primers described elsewhere ([Klindworth A](http://www.ncbi.nlm.nih.gov/pubmed/?term=Klindworth A%5BAuthor%5D&cauthor=true&cauthor_uid=22933715),[Nucleic Acids Res.](http://www.ncbi.nlm.nih.gov/pubmed/22933715) 2013). We will performed library preparation followed by Illumina sequencing according to standard protocols described previously (Caporaso JG, [ISME J.](http://www.ncbi.nlm.nih.gov/pubmed/?term=Caporaso+JG%2C+Lauber+CL%2C+Walters+WA%2C+Berg-Lyons+D%2C+Huntley+J%2C+Fierer+N%2C+Owens+SM%2C+Betley+J%2C+Fraser+L%2C+Bauer+M%2C+Gormley+N%2C+Gilbert+JA%2C+Smith+G%2C+Knight+R.+2012.+Ultra-high-throughput+microbial+community+analysis+on+the+Illumina+HiSeq+and+MiSeq+platforms.+2012.+ISME+J) 2012). The taxonomic composition of the intestinal microbiota will be characterized by grouping sequences into OTUs (Organizational Taxonomic Units).   Statistical analysis and bioinformatics:   - Student t test was used to assess differences between 2 mean values, and a Mann–Whitney U test was performed when data were not normally distributed. Either the x2 test or the Fisher exact test was used to test the degree of association of categorical variables. Statistical signiﬁcance was set at P , 0.05. Statistical analyses were performed using SPSS software version 20.0 (SPSS, Inc, Chicago, IL). - Microbiome Taxonomy Analyses & Bioinformatics: We used the QIIME open source algorithm for handling and interpretation of the data from the raw sequences; following quality assessment of sequence data, we assigned taxonomic affiliations using the RDP_classifier from the Ribosomal Database Project ( Wang, Q, Appl Environ Microbiol. 2007).   Ethics Committee  The study was approved by the Ethics Committee of Hospital del Mar Medical Research Institute, according to the principles expressed in the [Declaration of Helsinki](http://www.wma.net/en/30publications/10policies/b3/index.html) (annexed). Written informed consent will be obtained from all participants before enrollment in the study (annexed).  **Intervention:**  Aspects related to the investigational medicinal product (manufacture, labeling, distribution ...)  Probiotic: Trade name: Ultra - Levura ® lyophilized   - Responsible for manufacturing: BIOCODEX. - Drug marketed and distributed in Spain by Zambon Laboratories S.A. - Presentation: container with 50 capsules. - quantitative composition: Each capsule contains 1,000 million live bacteria (107) *Saccharomyces boulardii 17* lyophilised: 56.5 mg. Excipients: Sucrose (92.3mg), magnesium stearate q.s. - Laboratory Sales Price: 5.51 € / bottle of 50 tablets.   White Placebo: Sucrose   - Responsible for manufacturing: Kern Pharma   **Funding sources:** Helps independent clinical research of the Ministry of Health No. SPI / 2885/2011 |

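### The CD4/CD8 change endpoint is tested without adjustment for baseline count or CD4 group, which loses precision that a simple linear model would recover

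*Protocol*

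**What the plan says.** All of this is in the Protocol.

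- **Endpoint.** Study/Clinical Assessment lists "Changes in immune status (T-CD4+ and T-CD8+ lymphocyte count) and HIV-viral load" among the secondary endpoints. The primary endpoint is change in serum LBP. Immune reconstitution is named in the title and in the principal objective.
- **Measurement times.** "subjects will be visited at baseline (start of treatment), at week 12 (treatment discontinuation), and at week 24 (3 months after discontinuation of treatment". The sampling statement agrees: "Extraction of blood samples and stool collection will be performed before starting probiotics (baseline) at 3 and 6 months". So one pre-treatment study sample is planned. Screening for eligibility is mentioned, but no CD4 draw separate from baseline is described.
- **Test.** The statistical section names Student's t test for two means, or Mann-Whitney for non-normal data. It names no covariate and no stratification by CD4 group. The Summary describes the analysis as a before-and-after comparison.
- **Earlier counts.** Group 2 is defined by an "unfavorable persistent immunologic response (T-CD4+ cells <350 cells per microliter) despite long-term suppressed viral load (4-7 years". Group 1 is defined as "Patients with CD4 +> 400 cells / ml and undetectable viral load for more than two years", where the history concerns viral load. Medical records are already a source: "Clinical and demographic data of the study patients will be collected from the medical records". Past CD4 counts are not among the listed variables.
- **Size.** 44 patients, 22 in each CD4 group, randomised 1:1. No SD, correlation, effect size or power is given for any endpoint.

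**The concern.** A CD4 count varies within a patient from one sample to the next. Subtracting one baseline count from one follow-up count puts that variation into the endpoint twice. A model that estimates the baseline slope, rather than fixing it at 1 as a change score does, never has larger residual variance in large samples and usually has less.

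Precision is scarce here: about 22 patients per arm overall and about 11 per arm within each CD4 group. The CD4/CD8 count is the direct measure of the immune status that the title and principal objective refer to. Precision obtained from data already collected costs no extra patient, visit or sample. What is at stake is the width of the confidence interval for the arm difference. The planned comparison does not bias the randomised contrast.

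**Working it through.** **Inputs from the Protocol.** N = 44, allocation 1:1, one baseline, follow-up at weeks 12 and 24, a change endpoint, a two-sample test without covariates. The sample size has no stated derivation, so there is no precision figure to reproduce; only 22 + 22 = 44 can be checked.

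**Assumed inputs.** The correlation rho between counts of the same patient within a CD4 group, taken as 0.5 to 0.8; the number k of pre-treatment counts, 1 to 4; equal variance s² at every time.

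**Step 1: change score against adjustment for the one baseline count.**
- Variance of the change score: 2s²(1 − rho).
- Residual variance after adjustment: s²(1 − rho²).
- Ratio: (1 + rho)/2, a reduction of (1 − rho)/2.

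| rho | variance reduction | SE reduction | 44 patients equivalent to |
|---|---|---|---|
| 0.8 | 10% | 5% | 44/0.90 = 48.9 |
| 0.7 | 15% | 8% | 44/0.85 = 51.8 |
| 0.6 | 20% | 11% | 44/0.80 = 55.0 |
| 0.5 | 25% | 13% | 44/0.75 = 58.7 |

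These are large-sample figures. Estimating the slope inflates the variance by about 1 + 1/(N − 4) for a normal covariate: 1 + 1/40 = 1.025 with 44 patients, 1 + 1/18 = 1.056 with 22. At rho 0.8 the net reduction is then 1 − 0.90 × 1.025 = 8% overall and 1 − 0.90 × 1.056 = 5% within one CD4 group. At rho 0.5 it is 23% and 21%.

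**Step 2: adjustment for the mean of k pre-treatment counts, equal correlation at all time gaps.**
Residual variance is s²[1 − k·rho²/(1 + (k − 1)rho)]. The reduction against the single-baseline change score is:

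| rho | k = 2 | k = 3 | k = 4 |
|---|---|---|---|
| 0.8 | 27.8% | 34.6% | 38.2% |
| 0.7 | 29.4% | 35.4% | 38.7% |
| 0.6 | 31.2% | 36.4% | 39.3% |
| 0.5 | 33.3% | 37.5% | 40.0% |

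A change score taken from the mean of k counts, without a model, has variance proportional to 1 + 1/k against 2: 25%, 33% and 37.5% less for k = 2, 3, 4, whatever rho is. Together these give roughly 25% to 40% in variance. On the SE scale the ends are 1 − √0.75 = 13% and 1 − √0.60 = 23%.

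**Step 3: what the older counts add beyond Step 1.** Against single-baseline adjustment, the mean of 2 to 4 counts cuts variance by a further 11% to 20% at rho 0.5 and 20% to 31% at rho 0.8. Part of the 25% to 40% therefore comes from adjustment alone, most of it at low rho: at rho 0.5, 25 of the 40 points.

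**Step 4: if correlation fades with time.** Counts 6 months apart; variance split into a stable part, a serially correlated part (decay per quarter) and noise; 2 to 4 counts; outcome at week 12 or week 24; reduction against the single-baseline change score.

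| Stable / serial / decay | baseline only | mean of 2 to 4 counts |
|---|---|---|
| 0.6 / 0.2 / 0.7 (mild) | 13% to 15% | 20% to 26% |
| 0.4 / 0.4 / 0.8 (stronger) | 14% to 17% | 9% to 20% |

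Under the stronger decay, four counts at week 12 do slightly worse than baseline adjustment alone. In the extreme case of purely serial correlation with no noise (0 / 1 / 0.8), averaging is worse than the plain change score at week 12, while adjustment for the baseline alone still cuts variance by 10%.

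**The case against.** The strongest reply is that this is a pilot trial with LBP as its primary endpoint, that a t test on change from one baseline is conventional and valid, and that covariates and the definition of baseline are often left to a SAP, which is not shown. Most of this stands. The point is one of efficiency on a secondary endpoint; it is neither an error nor a contradiction. But the Protocol is not silent on the method: it names the tests, and they are unadjusted. A SAP that already specifies the adjusted model would settle the matter.

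A second reply is that older counts may not exist or may not help. That also stands in part. A reader might infer from the long suppression history that several CD4 counts are on file for everyone. The Protocol supports this for Group 2, since persistence over years cannot be shown by one count, but for Group 1 it requires only a viral-load history. A separate screening count cannot be assumed either. How many counts exist, and how far apart, is unknown.

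Two further stronger readings fail. One is that the plan throws away a quarter to two fifths of its precision outright. That figure concerns variance, needs 2 or more comparable counts per patient and a stable level, and includes gain that baseline adjustment gives without any past count. The other is that CD4 is the trial's least precise endpoint. No SD is given for any endpoint, so no such ranking can be made.

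**Conclusion.** The point holds as an efficiency recommendation. The planned unadjusted comparison of CD4/CD8 change is unbiased but less precise than a linear model on the same data. Adjustment for the single baseline count cuts variance by about 10% to 25% under assumed rho of 0.8 to 0.5, slightly less after the cost of estimating the slope. This part needs no past counts, and in large samples it cannot do worse than the change score.

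A covariate averaged over 2 to 4 pre-treatment counts raises the reduction to roughly 25% to 40% (SE about 13% to 23%). That part is conditional on such counts being on file, on an unchanged regimen and on roughly stable levels. The entry criteria favour stability (suppressed viral load for at least 2 years, no regimen change in the previous 2 years) but do not establish it for CD4. With fading correlation the total was 9% to 26% in the two cases with a stable component, and in the purely serial extreme averaging can lose precision. The values of rho and k are assumptions; the Protocol gives neither.

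**What to change.** 1. Replace the two-sample test for CD4 and CD8 by a linear model for the count at week 12, and likewise at week 24, with arm, baseline count and CD4 group (1 or 2) as terms. Report the adjusted arm difference with its confidence interval. This uses only data already planned.
2. Where recent routine counts under the same stable regimen are on file, use the mean of the baseline count and those counts as the covariate. Keep the baseline count in the mean and prefer recent counts, because old ones can add noise if levels drift. Patients without earlier counts keep their baseline value.
3. Fix the rule before unblinding: how many earlier counts, how far back, and from which laboratory, applied identically in both arms.

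The cost is one model statement and, for step 2, a few extra fields extracted from the records; no new visit or sample. The downsides are the assumption of roughly stable pre-treatment levels and a covariate that may be less precise in Group 1 if fewer counts are available there. If extraction proves impractical, step 1 alone is still worth making.

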**INDEPENDENT CLINICAL RESEARCH PROJECT: PROTOCOL**

|  | File nº |
| --- | --- |
|  | **SPI/2885/2011** |
| **TITLE: Treatment with probiotics (*Saccharomyces boulardii*) and its role in bacterial translocation and immune reconstitution in HIV infection** | |
|  | |
| Principal Investigator: **[name]** | |
| SUMMARY (Objectives and methodology):  **Objectives:** MAIN: To evaluate the parameters of bacterial translocation after treatment with probiotics (*Saccharomyces boulardii*) in HIV+ patients and its role on immune reconstitution. SECONDARY OBJECTIVES: 1) To analize the progress of immune activity markers after the administration of probiotics. 2) To determine the improvement of CD4+ lymphocytes and HIV viral load in patients after taking probiotics.  **Methods:** Design: A prospective randomized open controlled doble-blinded trial, to be performed at a tertiary care hospital in Barcelona. Subjects: Cronic HIV infected patients. Sample size: 44 cases. They´ll be divided in 2 groups: (1) Patients with CD4 +> 400 cells / ml and undetectable viral load for more than two years (22 cases) and (2) Patients with inmunodiscordancy, defined as patients with CD4 + T cells lower than 350 cells / ml despite 4-7 years of effective antiretroviral therapy. (22 cases). Intervention: Patients were randomized in 2 subgroups: (A) they´ll receive daily oral supplementation with *S. boulardii* for 3 months and (B) they ´ll receive placebo. Variables: bacterian lipopolisacarid levels (LBP), parameters of immune activation in plasma (sCD14, IFN-Υ, TNF, IL-2, IL-5, IL-6, IL-12) and fecal microbiome prior to the use of probiotics (baseline), at 3 and 6 months. Immunological and clinical data. Outcome measures: quantification of bacterial translocation levels, markers of activity and 16S rDNA gene amplification and parallel sequencing of fecal microbiome. Analysis: Comparison of variables before and after the intervention. The analysis will be performed by biological and immunological effectiveness. | |

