**INDEPENDENT CLINICAL RESEARCH PROJECT: PROTOCOL**

|  | File nº |
| --- | --- |
|  | **SPI/2885/2011** |
| **PI: [name]** | |
| **Hypothesis**      Oral supplementation with probiotic *Saccharomyces boulardii* decreases enteropathy associated with HIV infection, and consequently, minimizes microbial translocation and chronic immune activation. | |
| **Objectives:**  Principal:  To evaluate the changes on bacterial translocation, systemic inflammation and gut microbiome after treatment with probiotic *(Saccharomyces boulardii)* compared with placebo in HIV-positive patients under an effective ART and its role on immune reconstitution.  Secondary objectives:  1) To analyze the changes in immunoactivity markers after administration of probiotics and their relationship with bacterial translocation.  2) To explore if the immunological non-response was associated with higher systemic inflammation and microbial translocation parameters and a different gut microbiome pattern. | |

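### Stool may wait up to 24-48 hours before freezing, with no holding condition and no recorded times: added noise in the randomised microbiome comparison, possible bias in the within-arm and CD4-group comparisons

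*Protocol*

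**What the plan says.** Protocol, Methods, Procedure: "All patients also provided 50gr of stool samples at each visit (Baseline, week 12 and week 24"), and these samples are ones "which will be stored at -80°C within the first 24-48 hours". Their stated purpose is "to compare gut microbiome composition before and after a 12-week treatment with probiotic or placebo". The Fecal Microbiome Analyses item adds that "DNA will be extracted from frozen stool samples and amplified by PCR targeting 16S gene regions".

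The same Procedure list is precise about blood: "Within 30 minutes after puncture, blood was centrifuged at 3000 rpm for 15 minutes". For stool before freezing it gives no temperature, preservative or transport condition, and it does not say whether the clock starts at passage or at hand-over. The list of variables to be collected covers stool habit, medication, adverse events and adherence, but no stool passage or freezing time.

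The microbiome appears in three roles:
- Principal objective: "To evaluate the changes on bacterial translocation, systemic inflammation and gut microbiome after treatment with probiotic". The sentence goes on to name placebo as the comparator.
- Secondary objective 2: whether immunological non-response goes with "a different gut microbiome pattern", which compares the two CD4 groups.
- Secondary endpoint under Study/Clinical Assessment. The primary endpoint there is change in serum LBP.

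The Summary describes the analysis as "Comparison of variables before and after the intervention".

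**The concern.** The stool rule cannot be applied uniformly. A sample frozen at 30 hours meets the upper figure and misses the lower one. One patient's baseline stool may be frozen within hours and the week 12 stool after nearly two days at room temperature, and both comply.

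Until it is frozen, stool is living material, and 16S profiles are relative abundances, so delay and temperature can alter the quantity being measured. The choice of -80°C storage shows that the authors regard preservation as important. Shipping all samples in one frozen batch controls differences that arise after freezing, not before.

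Two kinds of harm need to be kept apart. Delay that varies haphazardly makes change scores noisier. Delay that differs systematically between visits, or between Group 1 and Group 2, shifts the mean and can pass for a change or a group difference. Because the times are not recorded, no later analysis, whatever an analysis plan may say, could adjust for them.

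**Working it through.** The protocol gives no drift rate, power or effect size for the microbiome, so there is no figure of its own to reproduce. What follows is conditional on assumptions.

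**Inputs from the protocol:** 44 patients, 22 per CD4 group and 22 per randomised arm; three stool collections each (44 × 3 = 132 stools); upper limit 48 hours; significance level 0.05.

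**Assumptions:** composition is summarised by one score; drift is linear at g SD per 24 hours and the same in all patients; tests are two-sided.

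**1. Haphazard delay.** Take the SD of change without holding as 1 and delays as uniform on 0 to 48 hours at each visit.
- Variance of one delay: 48²/12 = 192 h². Variance of the difference between two visits: 2 × 192 = 384 h².
- Added variance of change: 384 × (g/24)² = (384/576) × g² = 0.667 × g².
- Effective patients per arm: 22/(1 + 0.667 × g²).

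| g (SD per 24 h) | Added variance | Effective n of 22 |
|---|---|---|
| 0.1 | 0.7% | 21.9 |
| 0.25 | 4.2% | 21.1 |
| 0.5 | 16.7% | 18.9 |

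A simulation of 4,000 trials agrees. At g = 0.5 the average sample SD of change rises from 0.99 to 1.07, and (1.07/0.99)² = 1.17. False-positive rates stay near 5% within an arm and between arms, so there is no bias.

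In terms of detectable difference at 80% power (also an assumption), 22 per arm gives (1.96 + 0.84) × √(2/22) = 0.845 SD. Added variance of 16.7% raises this to 0.845 × √1.167 = 0.91 SD.

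**2. Systematic delay.** Same simulation with no true effect and 22 per group. For the first two columns of rates, baseline delay is uniform on 0 to 24 hours and week 12 delay on 24 to 48 hours, in both arms alike. For the last column, Group 1 delay is uniform on 0 to 24 hours and Group 2 on 24 to 48 hours at a single visit, in units of the between-patient SD.

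| g (SD per 24 h) | False shift | Within-arm before-after | Between randomised arms | Group 1 vs Group 2 |
|---|---|---|---|---|
| 0 | 0 | 5.2% | 4.9% | 5.3% |
| 0.1 | 0.10 SD | 7.3% | 4.9% | 5.7% |
| 0.25 | 0.25 SD | 20.2% | 5.1% | 13.1% |
| 0.5 | 0.50 SD | 59.4% | 4.7% | 35.3% |

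Entries under the last three columns are false-positive rates at nominal 5%, with a simulation error of about √(0.05 × 0.95/4000) = 0.3 percentage points near that level. A delay shift common to both arms cancels in the between-arm comparison of change. It does not cancel within one arm, and a delay gap between the CD4 groups does not cancel in their comparison.

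**The case against.** The strongest reply is that the main microbiome question is a randomised one. The principal objective names placebo as comparator, and participants and care providers are blinded, so handling is balanced between arms in expectation. This stands, and the table confirms it. A reader might infer that holding drift could be mistaken for a probiotic effect. For the between-arm comparison of change the document does not support that; the harm there is noise.

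A second reply is that any large loss of information is conjecture. This also stands. A reader might suppose that the effective sample could be halved, from 22 to 11 per arm. On the model above that needs 0.667 × g² = 1, or g of about 1.2 SD per 24 hours, and nothing in the document suggests such a rate. Nor does it say that Group 1 and Group 2 deliver stool differently, or where stool is collected. Systematic delay is something the rule permits, not something shown to occur.

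Third, holding temperature and time stamps often sit in a laboratory procedure, and Phase 1 of the Workplan includes a check of the sample-handling pathway. This stands only in part. The check sets no conditions, no laboratory procedure is cited for stool collection, and this protocol itself chose to fix a time limit for stool and fixed it as a range. The 30-minute blood rule concerns a different material and does not contradict the stool window; it shows only that pre-analytical limits were considered to belong in this document.

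Finally, serum LBP is unaffected, the study is described as a pilot, and secondary objective 2 is exploratory. All true, and this limits the weight of the point.

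**Conclusion.** The point holds in a limited form. The stool rule is loosely fixed: a range in place of a limit, no holding condition and no recorded times. For probiotic versus placebo the consequence is added noise. It is about 17% more variance, or about 19 effective patients out of 22 per arm, if delays are uniform over 0 to 48 hours and drift is 0.5 SD per 24 hours, and less at slower drift. Bias is possible only in within-arm before-after readings and in the non-randomised Group 1 versus Group 2 comparison, and only if delays differ systematically. With a 24-hour gap and drift of 0.1 to 0.5 SD per 24 hours, false-positive rates would be about 7% to 59% and 6% to 35% respectively. The drift rates are assumptions; the document gives none. The primary endpoint is untouched. The change is worth making before collection starts, because unrecorded delays cannot be recovered.

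**What to change.** - Replace the 24-48 hour wording with one maximum time from passage to freezing and one cold holding condition, identical at all three visits and in both CD4 groups. A limit of 24 hours would serve as an example; it is the lower end of the present range and has no other basis in the document.
- Record the time of passage and the time of freezing for every sample.
- Flag samples over the limit but do not re-collect them. Treatment starts at baseline and stops at week 12, so a later replacement could fall after the first dose or after the last one and distort the very contrast it is meant to protect.
- Repeat the microbiome comparison excluding flagged samples or adjusting for holding time.
- State that the treatment conclusion on the microbiome rests on the between-arm comparison of change, with within-arm changes as description only.

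Cost: a wording change, two form fields, cool packs and a few flagged samples.

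### Change in LBP is to be compared by an unadjusted t test or Mann-Whitney test; one pre-named ANCOVA on baseline LBP and CD4 group would be more precise using data already collected

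*Protocol*

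**What the plan says.** The Protocol, under Study/Clinical Assessment, defines the primary endpoint: "The primary end point of the study will be changes in serum LBP levels as a marker of microbial translocation". The visit is not named in that sentence. Blood is taken at baseline, at week 12 (end of treatment) and at week 24.

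Under Statistical analysis and bioinformatics, the rule for continuous variables is general and is not tied to LBP: "Student t test was used to assess differences between 2 mean values", with a Mann-Whitney alternative where the "U test was performed when data were not normally distributed". Chi-square or Fisher tests cover categorical variables. The significance level is 0.05. The section gives no covariate, model, measurement scale or criterion for judging normality.

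The design has two CD4 groups of 22 patients. Under Randomization: "Patients in both groups (1 and 2) will be randomized in 2 subgroups", with 22 patients per arm overall. Secondary objective 2 treats CD4 response as possibly related to the outcome: "To explore if the immunological non-response was associated with higher systemic inflammation and microbial translocation parameters".

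**The concern.** Every patient has a baseline LBP value and a known CD4 group before treatment starts. The stated tests use neither as a covariate. If they are applied to change scores, baseline is subtracted with a fixed coefficient of 1. When the correlation between visits is well below 1, that overcorrects and carries baseline noise into the outcome. With 22 per arm, this avoidable variance can decide whether an effect is visible.

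The second issue is that the test depends on how the observed data look, by an unstated criterion. A t test speaks to a difference in means and a Mann-Whitney test to a comparison of ranks. The quantity that the primary result estimates is therefore not fixed in advance.

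**Working it through.** **The plan's own figure.** The summary states "Sample size: 44 cases" without an effect size, SD or power, so 44 cannot be reproduced. As a reference, 22 per arm at two-sided 5% gives 80% power for about 0.86 SD of whatever variable is tested (noncentral t, 42 df).

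**Inputs.** From the Protocol: n = 22 per arm, 1:1 allocation, alpha 0.05. Assumed, because the Protocol does not give them: two-sided testing, equal LBP SD at both visits, no dropout, a correlation ρ between baseline and week 12 of 0.3 to 0.9, and an illustrative true effect of 0.6 LBP SD.

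**Variance of the treatment effect**, in units of 2σ²/n:
- t test on change: 2(1 − ρ)
- ANCOVA on baseline: 1 − ρ²
- ratio of ANCOVA to change: (1 + ρ)/2

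Estimating the slope costs a factor of 1 + 1/(2n − 4) = 1 + 1/40 = 1.025. At ρ = 0.5 the ratio is 0.75, or 0.75 × 1.025 = 0.769 with the penalty.

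**Power.** The noncentrality is d/√(2v/n), where v is the variance factor, with 42 df for change and 41 for ANCOVA. At ρ = 0.5 and d = 0.6:
- change: v = 1.00, standard error √(2/22) = 0.302, noncentrality 1.99, power 49%
- ANCOVA: v = 0.769, standard error √(1.538/22) = 0.264, noncentrality 2.27, power 60%

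| ρ | Variance reduction | After penalty | Detectable at 80% power, change / ANCOVA (SD) | Power for 0.6 SD, change / ANCOVA | Total N for change to match ANCOVA on 44 |
|---|---|---|---|---|---|
| 0.3 | 35% | 33% | 1.02 / 0.84 | 38% / 52% | 68 |
| 0.5 | 25% | 23% | 0.86 / 0.76 | 49% / 60% | 59 |
| 0.7 | 15% | 13% | 0.67 / 0.63 | 71% / 77% | 52 |
| 0.9 | 5% | 3% | 0.39 / 0.38 | 99% / 99% | 46 |

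The last column is 44 × 2(1 − ρ)/(1 − ρ²), before the penalty. A simulation of 3,000 runs per setting agreed: change against ANCOVA gave 38% and 53%, 49% and 59%, 70% and 76%, 99% and 99%. With the penalty, ANCOVA loses its advantage only above ρ = 2/1.025 − 1 = 0.95.

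**CD4 group.** Adding it to the ANCOVA moved simulated power by about 1 point or less, even with the groups 0.5 SD apart (for example 58.0% to 58.6% at ρ = 0.5). A constant level difference between groups cancels in the change. The term helps only so far as it explains variance in the tested variable: the detectable difference goes from 0.865 to 0.843 SD if it explains 5%, and to 0.821 SD if 10%.

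**Choosing the test from the data.** This was simulated under the null with a 5% Shapiro-Wilk test in each arm (6,000 runs, simulation error about 0.3 points). Type I error was 5.3% for normal data and 5.0% for lognormal data.

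**The case against.** The strongest reply is that an unadjusted test on change is valid in a randomised trial, that the Protocol calls this a pilot with no power target, and that covariates, transformations and normality criteria usually belong in a SAP, which is not at hand. The statistics section is also generic and assigns no test to LBP. Much of this stands. The point concerns efficiency, and an unseen SAP may already contain a covariate model. What remains is that the Protocol does not merely stay silent: it names unadjusted tests and a rule for switching between them, and it sets a significance level.

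Some stronger readings are tempting but not supported:
- *Baseline LBP is ignored.* The endpoint is a change, so baseline is used by subtraction. Comparing ANCOVA with a t test on week-12 values alone would measure it against an analysis that the Protocol does not state for LBP.
- *Leaving out CD4 group is costly.* Secondary objective 2 only sets out to explore a difference in marker levels, and a constant difference cancels in the change. Nothing in the Protocol says that the groups change differently.
- *Choosing the test from the data inflates type I error.* The simulation shows that it does not.
- *The arms may be unbalanced within CD4 groups.* The Protocol says "A computer-generated randomization list will be used" and never uses the word stratified, but its text fairly reads as randomisation within each group. Imbalance figures for a single unstratified list would contradict that reading.

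**Conclusion.** The point holds as a gain in precision that needs no new data. Relative to a t test on change, ANCOVA lowers the variance of the treatment effect by about 35% at a correlation of 0.3 and 5% at 0.9 (33% to 3% after the small-sample penalty). The gain is material at low to moderate correlation and negligible at 0.9. Nearly all of it comes from baseline LBP; the CD4 term adds little, but makes the analysis match the randomisation. Because the correlation is unknown, the size within this range cannot be fixed from the Protocol.

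Separately, the primary result should not be left open between a mean difference and a rank comparison. That is a matter of what is estimated, not of error control. Neither point makes the planned test invalid. The figures rest on equal SDs, no dropout, two-sided testing and the illustrative 0.6 SD effect.

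**What to change.** Name one primary analysis in the Protocol before unblinding: ANCOVA of week-12 LBP on arm, baseline LBP and CD4 group, reported as an adjusted effect with a 95% CI. Fix the scale at the same time. Log is one option, giving a ratio of geometric means, but the Protocol has no information on the distribution of LBP that would settle it. On a given scale, the arm effect is the same whether week-12 LBP or its change from baseline is the response, so the endpoint need not be redefined. Replace the switch to Mann-Whitney by a rank-based ANCOVA as a pre-stated sensitivity analysis. Use the same model for the other continuous markers. If a SAP already specifies such a model, align the Protocol with it.

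The cost is a change of wording and two model degrees of freedom (residual 42 to 40). No further samples or patients are needed.
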